### Statistical analysis

All analyses will be conducted with R statistical software (Version 3.6.1; R Core Team, 2019) and SPSS for Windows, V.27.0 (IBM Corp, released in 2017, IBM SPSS Statistics, Armonk, New York, USA). After determining the amount and patterns of missing data (missing completely at random, missing at random or missing not at random), any missing values will be imputed using ‘multivariate imputation by chained equations’.

Primarily, MACE will be analysed by survival analysis in which the RISE intervention group will be compared with standard care. Cox proportional hazards model will be used, as this provides insights into the effectiveness as well as the effect size of the RISE intervention.

For the economic evaluation, differences in costs and effects will be estimated, while appropriately accounting for ‘baseline imbalances’, ‘correlated costs and effects’, ‘skewed costs and/or effects’, ‘missing data’ and ‘clustered data’, if applicable.^46^ Then, ‘incremental cost-effectiveness ratios’ will be calculated by dividing the estimated difference in costs by those in effects. Uncertainty regarding the RISE intervention’s cost-effectiveness will be graphically illustrated using ‘cost-effectiveness planes’ and ‘cost-effectiveness acceptability curves’. The latter indicates the probability of the intervention being cost-effective compared with usual care for different values of willingness to pay (ie, amount of money decision-makers are willing to pay per unit of effect gained).^47^ To test the robustness of the results, various sensitivity analyses will be performed (eg, complete-case analysis).^48^

The 24-hour movement behaviour consists of sleep quantity, sedentary time, MPVA and LPA. Participants will wear the ActivPAL accelerometer for eight consecutive days during T0, T1, T2 and T4. Daily estimates will be derived from ActivPAL data using the newest R package GGIR.^49^ Within the compositional data analysis (CoDA), SB, MVPA, LPA and sleep quantity are considered as proportions that sum up to 1 (eg, 24 hours).^50^ The raw accelerometry data will be converted into a compositional dataset using the GGIR package. Isometric log-ratios will be used to map the compositional dataset into real-valued coordinates, allowing standard statistical methods to be used. The compositional dataset will be analysed using multivariate analysis of variance (MANOVA) testing overall differences in 24-hour movement patterns between the control and experimental groups. Compositional differences will be calculated via perturbation and visualised using ternary plots.^51^ The usage of CoDa and MANOVA is strongly favoured over traditional analytical techniques when analysing movement behaviours.^52^

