## Methods

In this assessor-blinded multicentre randomised controlled trial, participants who require secondary prevention based on their 24-hour movement behaviour (further explained at ‘Study procedures’) will be included and randomly assigned to either the experimental or control group (allocation ratio 1:1) (figure 1). For the protocol, the Standard Protocol Items: Recommendations for Interventional Trials checklist was used, including trial registration details (table 1).

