### Study procedures

After obtaining informed consent (online supplemental file 1), baseline measurement (T0) takes place at the participants’ home (figure 1). During this visit, an activity monitor will be provided to objectify the 24-hour movement behaviour. If participants require secondary prevention, it will be based on their 24-hour movement behaviour pattern^11^: *sedentary prolongers,* ≥9.5 hours of sedentary time per day, >50% of the sedentary time is spent in bouts >30 min and not reaching the physical activity guideline (150 min MVPA during the week); *sedentary movers,* <9.5 hours of sedentary time and (1) ≤50% of the sedentary time spent in bouts >30 min or (2) not reaching the physical activity guideline.^16 17^ Randomisation will take place for *sedentary prolongers* and *sedentary movers,* with stratification according to these two profiles. All other participants will be excluded after baseline measurement.

Concealment of allocation will be ensured by individual randomisation by an independent researcher. Randomisation to either the experimental or control group will be done using a computer-generated random sequence with block sizes of two, four and six (Castor Electronic Data Capture 2021, Ciwit B.V., Amsterdam, The Netherlands).

The experimental group receives the RISE intervention from a trained primary care physiotherapist for 15 weeks. Follow-up measurements take place at the end of the intervention period (T1) (ie, 4 months post randomisation) and at 6 months (T2), 9 months (T3) and 12 months post randomisation (T4) (figure 1). Due to the nature of the intervention, participants and primary care physiotherapists will not be blinded for treatment allocation. The researcher who performs the measurements at T1 is blinded to treatment allocation.

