The intervention will be delivered by ±130 primary care *RISE physiotherapists* specialised in neurological care. All physiotherapists will be extensively trained in four sessions of 3–4 hours focused on behaviour change techniques, the RISE protocol and motivational interviewing. The training is accredited by the Royal Dutch Society for Physiotherapy. After the training, physiotherapists will join an online learning community, where RISE-related questions or cases will be shared during 3-monthly booster sessions. Physiotherapists make use of the following behaviour change techniques: goal-setting (on behaviour and outcome), action planning, social support, self-monitoring of behaviour, feedback on behaviour, discrepancy between current behaviour and goals, information about health consequences, problem-solving, restructuring the social environment, prompts and cues, habits formation and instructions how to perform the behaviour^21^ (table 2).

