### Control group (usual care)

There will be no restrictions for receiving other care as usual. Participants in the experimental and control group receive usual care according to national stroke guidelines.^18^ At T1–T4, participants are asked about all of their healthcare utilisation via the institute for Medical Technology Assessment (iMTA) Medical Consumption Questionnaire (iMCQ) (^22^).

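### Physiotherapist nesting in the experimental arm is not allowed for in the Cox model or the MANOVA: a minor, cheap improvement that matters mainly for movement behaviour

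*Protocol article*

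**What the plan says.** The Study procedures section of the protocol article fixes the unit of randomisation as the participant: "Concealment of allocation will be ensured by individual randomisation by an independent researcher". It then states: "The experimental group receives the RISE intervention from a trained primary care physiotherapist for 15 weeks". The section on the experimental group gives the number of therapists: "The intervention will be delivered by ±130 primary care" physiotherapists. Controls have no RISE therapist. Their section says only that they receive guideline-based usual care and that "There will be no restrictions for receiving other care as usual".

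Under Statistical analysis, the primary comparison of MACE is described in two sentences, the second being "Cox proportional hazards model will be used, as this provides insights into the effectiveness as well as the effect size of the RISE intervention". The movement-behaviour composition is transformed to isometric log-ratios and analysed by "multivariate analysis of variance (MANOVA) testing overall differences in 24-hour movement patterns between the control and experimental groups". Neither description names a therapist term, a frailty or random effect, or a robust variance. Clustering is named once in that section, in the paragraph that begins "For the economic evaluation, differences in costs and effects will be estimated, while appropriately accounting for". There, clustered data is one item in a list of issues to be handled if applicable.

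**The concern.** The design is partially nested. Participants in the experimental arm share therapists, while each control stands alone. The active ingredient is personalised coaching, and the Discussion treats therapist training and adherence to the protocol as things that have to be secured, so delivery can vary between therapists. If it does, outcomes of participants coached by the same therapist are positively correlated. A variance that ignores this is then too small, and the confidence interval for the treatment effect is too narrow.

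The two analyses are not equally exposed. A Cox model can carry a cluster-robust variance and remain the model named. An ordinary MANOVA assumes independent observations, so the named method itself leaves the nesting out. Movement behaviour is also the outcome that the therapist directly coaches, so a therapist effect is more plausible there than for MACE.

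**Working it through.** **1. The plan's own figure.** The Sample size section gives 752 participants (376 per arm) for a two-sided log-rank test at 0.05 with power 0.85, one-year event-free proportions of 0.80 and 0.87, accrual over 1.5 years, one further year of follow-up and 20% loss in each arm. The Lachin-Foulkes formula with exponential survival, uniform accrual, a total duration of 2.5 years and 20% yearly loss gives N = 750.6, or 752 in two equal arms. The figure therefore reproduces with independent participants and contains no design effect.

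**2. Formulas.**
- Mean caseload: m = 376/130 = 2.89.
- Size-weighted caseload: m' = m(1 + CV²), where CV is the coefficient of variation of caseloads. This is 2.89 for CV 0, and 2.89 × 1.49 = 4.31 for CV 0.7.
- Design effect in the experimental arm: DE = 1 + (m' − 1) × ICC. In the control arm it is 1.
- Under the null the two arms carry equal weight, so the variance ratio of the contrast is (DE + 1)/2. The true standard error is the square root of that ratio times the naive one.
- Actual two-sided alpha = 2 × [1 − Φ(1.96/SE ratio)].

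ICC and CV are assumptions; the documents give neither.

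**3. A plausible ICC for MACE.** The Sample size section assumes 13% MACE at one year in the experimental arm, so the binary variance is 0.13 × 0.87 = 0.1131. An ICC of 0.05 implies a between-therapist SD of √(0.05 × 0.1131) = 7.5 percentage points, and 0.10 implies 10.6. Both exceed the whole assumed effect of 7 points. A generous alternative lets therapists range uniformly from no effect (20% risk) to twice the assumed effect (6%). The SD is then 14/√12 = 4.0 points and the ICC is 0.0404²/0.1131 = 0.014.

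**4. Results.**

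| Analysis | ICC | CV | DE | SE ratio | Alpha |
|---|---|---|---|---|---|
| MACE | 0.01 | 0 | 1.019 | 1.005 | 0.051 |
| MACE | 0.014 | 0 | 1.026 | 1.007 | 0.052 |
| MACE | 0.014 | 0.7 | 1.046 | 1.012 | 0.053 |
| Movement, 376 per arm | 0.05 | 0 | 1.095 | 1.023 | 0.056 |
| Movement, 376 per arm | 0.05 | 0.7 | 1.165 | 1.041 | 0.060 |
| Movement, 376 per arm | 0.10 | 0 | 1.189 | 1.046 | 0.061 |
| Movement, 376 per arm | 0.10 | 0.7 | 1.331 | 1.080 | 0.069 |

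At ICC 0.01 with equal caseloads, power for MACE falls only from the planned 0.85 to 0.847.

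**5. Movement behaviour with 59 per group.** The Sample size section says 59 participants per group will be used for the sedentary-behaviour analysis, whereas Table 3 schedules the ActivPAL without such a limit. If 59 participants are spread at random over 130 therapists, the size-weighted caseload is 1 + 58/130 = 1.45. The SE ratio is then 1.006 at ICC 0.05 and 1.011 at ICC 0.10, with alpha 0.051 and 0.053.

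**The case against.** The strongest objection is that this is read from silence. The article gives the primary analysis two sentences and never says that participants are treated as independent. A Cox model with a cluster-robust variance still fits its wording, and a full protocol or analysis plan may specify one. This stands for the Cox model, and it is one reason why the point is minor. It has less force for the MANOVA, where independence belongs to the named method.

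A reader might infer that the article contradicts itself by handling clustering in the economic evaluation and not in the primary analysis. The text does not support that. The economic paragraph is a general list, hedged by applicability, and it names no cluster unit. It shows that clustering was thought of in one place; it does not commit to a therapist adjustment there.

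A reader might also infer a materially inflated error rate for MACE. Three things speak against it. ICCs of 0.05 to 0.10 are hard to believe for MACE (step 3). Weighting the arms by their expected events under the alternative would raise the worst-case alpha to 0.074, but type I error belongs to the null, where the arms weigh equally and the same case gives 0.069. Finally, if RISE changed nobody's outcome, therapists could not create correlation, and locality effects would fall on both arms under individual randomisation. The alpha figures therefore describe a zero average effect with real differences between therapists. Otherwise the consequence is interval width.

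The weekly protocol, the training and the booster sessions should also reduce variation between therapists. That is fair, and it argues for the lower end of the ranges.

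**Conclusion.** The point holds as a minor improvement. The nesting in one arm is explicit, and the descriptions of the Cox model and, more clearly, of the MANOVA make no allowance for it. With about 2.9 participants per therapist, the naive standard error for MACE is about 0.5 to 1% too small at an ICC of 0.01 to 0.014. This neither threatens the primary conclusion nor calls for a larger sample. For movement behaviour the true standard error is about 2 to 8% larger than the naive one if all 376 are analysed and the ICC is 0.05 to 0.10 with a caseload CV of 0 to 0.7; with 59 per group the error is about 1% or less. All these sizes rest on assumed ICCs and caseload spreads. The direction does not, provided the within-therapist correlation is positive.

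**What to change.** Record the treating physiotherapist for every RISE participant. Report the Cox hazard ratio with a cluster-robust variance, taking the physiotherapist as the cluster and each control as a cluster of one. Analyse the log-ratio coordinates with a physiotherapist random effect in the experimental arm only, or with the same robust variance.

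The robust variance leaves the hazard ratio itself unchanged; the interval will usually be slightly wider. Besides the analysis wording, the only other cost is one data item. The article does not say that the therapist's identity is stored with the trial data, but physiotherapists use a monitoring dashboard and complete the compliance measures, so it should be easy to obtain. No change to the sample size is needed.

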**Trial registration number:**

NCT06124248.

STRENGTHS AND LIMITATIONS OF THIS STUDYThe RISE (*Reduce and Interrupt sedentary behaviour using a blended behavioural intervention to Empower people at risk towards sustainable 24-hour movement behaviour change)* intervention integrates behaviour change techniques, the RISE eCoaching system, participatory support and extensively trained physiotherapists to promote sustainable movement behaviour change.All RISE physiotherapists will complete a 4-day course and participate in the RISE learning community (where RISE-related knowledge or cases will be shared during 3-monthly booster sessions) to ensure RISE intervention quality.The RISE intervention will be delivered in the home setting and is aligned with the existing healthcare system, enhancing its potential for future implementation within usual care.The use of repeated objective measurements will increase statistical power of the study.To address the potential limitation that individuals with limited digital health literacy may struggle to engage with the intervention, the application was co-designed with people with stroke to enhance usability, and participants receive coaching on how to use the RISE eCoaching system.

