	Inclusion criteria: if people are aged ≥18 years, had a first-ever symptomatic stroke (excluding transient ischaemic attacks) within 6 months before inclusion, are able to walk independently (functional ambulant category ≥3), were independent regarding activities of daily living pre-stroke (Barthel Index >18), are not participating in a physical rehabilitation programme lasting ≥3 months and are discharged to the home-setting.
	Exclusion criteria: if people are unable to understand the Dutch language or have severe comorbidities that withhold them from safely reducing and interrupting their sedentary time
Study type	Interventional
	Allocation: assessor-blinded multicentre randomised controlled trial
Date of first enrolment	November 2023
Target sample size	1000
Recruitment status	Recruiting
Primary outcome(s)	Effectiveness of the RISE intervention regarding prevention of MACE measured at 1 year post randomisation comparing experimental and control groups.
Key secondary outcomes	Cost-effectiveness of the RISE intervention for MACE prevention and quality adjusted life years.Changes in 24-hour movement behaviour (sedentary behaviour, physical activity and sleep) over time between the experimental and control group.

MACE, new major cardiovascular event or death; N.A., not applicable; RISE, Reduce and Interrupt sedentary behaviour using a blended behavioural intervention to Empower people at risk towards sustainable 24-hour movement behaviour change.

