### Secondary outcomes

Cost-effectiveness of the RISE intervention will be assessed for MACE prevention and QALYs. QALYs will be based on the participants’ responses to the Euro Quality of Life 5 Dimensions.^25^ These responses will be converted into utility values using the Dutch tariff, after which QALYs will be estimated using linear interpolation between measurement points.^26^ All costs related to the RISE intervention will be considered: that is, costs of the intervention, other healthcare utilisation, informal care, sports equipment and memberships, as well as losses from unpaid and paid work (ie, absenteeism and presenteeism). Intervention costs will be microcosted, meaning that detailed data will be gathered about the number and kinds of resources that are used while providing the RISE intervention, as well as information about their respective unit costs. All other kinds of resource use will be measured at T1–T4, using modified versions of the iMCQ and the iMTA Productivity Cost Questionnaire.^27^ Resource use will be valued in accordance with the Dutch manual for costing studies in healthcare.^22^

Change in 24-hour movement behaviour will be measured in the experimental and control group. The 24-hour (SB, physical activity and sleep) is measured with the ActivPAL (PAL Technologies Ltd, Glasgow, UK).^28^ This monitor is a combination of a triaxial accelerometer and inclinometer, worn on the anterior side of the unaffected thigh and detects if someone is either sedentary (sitting, lying or reclining), standing or walking. The ActivPAL is sealed in a waterproof sleeve and attached to the skin using hypoallergenic tape. Participants will be instructed to wear the ActivPAL for eight consecutive days. The first 24 hours of the data will be removed in order to counteract a possible Hawthorne effect.^29^ A valid day requires at least 10 hours of waking wearing time. Participants having at least three valid measurement days per time point will be used in the analysis.

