### Sample size

The required number of subjects was calculated using the Lachin and Foulkes Logrank Test module in the PASS 2008 software (Hintze J. PASS 2008, Kayesville, Utah, USA www.ncss.com). The power calculation was performed based on detecting a difference in MACE between the experimental and control group. In line with the effectiveness of cardiac rehabilitation, we expect that the RISE intervention will decrease the number of MACE by 35%.^43^ In the control group, 25% is expected to have MACE in the first year.^3 44^ To not underpower the study, an event rate of 20% in the control group in the first year is used. Participants will enter the study during an accrual period of 1.5 years. Enrolment is assumed to be completed for 50% when 50% of the accrual time has passed. A follow-up period of 1 year is assumed to have a 20% loss to follow from the experimental group and a 20% loss to follow from the control group. A two-sided log rank test with a power of 0.85 and a 0.05 significance level to detect a difference of 0.07 between 0.80 and 0.87 (the proportions surviving the experimental and control group after 1 year) led to an overall sample size of 752 participants (of which 376 are in the experimental group and 376 in the control group).

*Sedentary prolongers* and *sedentary movers* will be the target population of the study and will be randomised to the intervention or control group. From our RISE cohort study, we know that 67% of the participants with stroke were *sedentary prolongers* or *sedentary movers*.^11^ Therefore, we expect around 1000 participants need to be screened during baseline measurement (figure 1). Based on our pilot study, we expect to include 2–3 participants per hospital per month. With 20 participating hospitals, this will lead to the expected number of 762 participants by December 2025.

Our secondary outcome, effectiveness of the RISE intervention on reducing SB, can be assessed in a smaller population. From the RISE pilot study, we know that the target group had an average of 11 hours and 21 min of sedentary time per day, with an SD of 77 min/day.^14^ This means, with a two-sided significance level of 0.05, a power of 80%, that a sample size of 47 people per group is needed to detect a minimal detectable change of 45 min in SB between our groups.^45^ Accounting for a dropout rate of 20%, 59 participants per group will be used for this analysis.

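### The 59 per group for sedentary behaviour conflicts with the valid-data rule and the ActivPAL schedule, and the MANOVA names no visit, baseline or stratum term

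*Protocol article*

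**What the plan says.** **Outcome.** Table 1 of the protocol article lists as a key secondary outcome: "Changes in 24-hour movement behaviour (sedentary behaviour, physical activity and sleep) over time between the experimental and control group". The abstract also describes it as change over time. Secondary outcomes adds: "Change in 24-hour movement behaviour will be measured in the experimental and control group".

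**Data collection.** Under Statistical analysis: "Participants will wear the ActivPAL accelerometer for eight consecutive days during T0, T1, T2 and T4". Table 3 shows the same schedule, and neither place limits it to a sub-sample. Under Study procedures, the T0 recording decides who is randomised and defines the two sedentary profiles used for stratification. Among the article's strengths: "The use of repeated objective measurements will increase statistical power of the study".

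**Who is analysed.** Secondary outcomes admits anyone with three or more valid days at a time point. Sample size, having said that sedentary behaviour can be studied in fewer people than MACE, ends: "59 participants per group will be used for this analysis".

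**Test.** The only inferential method named for movement behaviour, applied to isometric log-ratio coordinates, is a "multivariate analysis of variance (MANOVA) testing overall differences in 24-hour movement patterns between the control and experimental groups".

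**The concern.** There are two linked problems.

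First, the article gives two different analysis sets. One is everyone with enough valid wear. The other is a fixed 59 per group, worded as what will happen and not as a minimum. Nothing says how the 59 would be chosen. Randomisation protects the comparison of the full groups. It protects a subset only if the rule for forming it is fixed in advance and does not depend on allocation or outcome. Participants and physiotherapists know the allocation here, so an open rule is undesirable.

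Second, the outcome is change across four measurement times, but the named test is described only as a comparison of two groups. A reader cannot tell whether it concerns T1, T2, T4 or all of them, or how T0 enters. The economic evaluation in the same section does say that baseline imbalance will be handled.

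At stake is the precision of the trial's main evidence on whether behaviour changed, and whether a smaller or fading effect at T2 and T4 could be seen.

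**Working it through.** **Inputs from Sample size:** SD of sedentary time 77 min/day, difference 45 min, two-sided 0.05, power 80%, dropout 20%, 376 randomised per group. The baseline-to-follow-up correlation rho is not given and is assumed below.

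**1. Reproduce the plan's figure.**
- Normal approximation: n = 2 × (1.960 + 0.842)² × (77/45)² ≈ 46 per group.
- The t-test version gives 46.94, so 47.
- Dropout: 47 / 0.80 = 58.75, so 59.

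Both stated figures reproduce. They are the size for an unadjusted comparison of sedentary minutes at one time point. No baseline correlation or repeated measurement enters.

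**2. Share of the trial.** 2 × 59 = 118, and 118 / 752 = 15.7% of those randomised.

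**3. Precision under the two readings.** 95% half-width = 1.96 × 77 × √(2/n). Full set: 376 × 0.80 = 300.8, so about 300 per group.

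| n analysed per group | Half-width (min/day) | Difference detectable at 80% power (min/day) |
|---|---|---|
| 47 (59 less dropout) | ±31.1 | 44.5 |
| 59 (no dropout) | ±27.8 | 39.7 |
| 300 (376 less 20%) | ±12.3 | 17.6 |

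The ratio 31.1 / 12.3 is about 2.5.

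**4. Gain from baseline adjustment at one follow-up visit.** The residual variance is 1 − rho² of the unadjusted variance, so the reduction is rho². The half-width is multiplied by √(1 − rho²).

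| Assumed rho | Variance reduction | Half-width, n = 47 | Half-width, n = 300 |
|---|---|---|---|
| 0.3 | 9% | ±29.7 | ±11.8 |
| 0.5 | 25% | ±27.0 | ±10.7 |
| 0.6 | 36% | ±24.9 | ±9.9 |
| 0.7 | 49% | ±22.2 | ±8.8 |

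**5. Is 47 the size for the named test?** No. Four behaviours give three log-ratio coordinates. Suppose these separate the groups by the same standardised distance as sedentary time alone, 45/77 = 0.584 (an assumption). A three-variable Hotelling test then has power of about 63% at 47 per group, 75% at 59 and over 99.9% at 300. So 59 is a minimum for sedentary minutes only, not for the MANOVA.

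**The case against.** The strongest reply is that the article is condensed. Covariates, visit coding and the stratification term commonly sit in a full protocol or analysis plan that is not shown. A reader might infer that the MANOVA excludes baseline and time and so cannot estimate change. The text does not support that. A MANOVA can be run on change scores or with visit as a within-person factor, the four visits are listed in the same paragraph, and the planned perturbation differences could express change between visits. An unadjusted group comparison at follow-up is also valid under randomisation. What stands is narrower: the one test described for a change outcome names no visit and no use of T0 or profile.

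A reader might also infer that the MANOVA itself will be run on 59 per group. The documents do not say so. The 59 is attached to sedentary behaviour under Sample size, and Statistical analysis sets no subset and plans imputation of missing values. The figure may be a loosely worded minimum. Even so, sedentary time is part of the composition, no separate analysis of it is described, and the literal wording conflicts with the valid-day rule.

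Two further inferences go too far. Nothing suggests that the 59 would be picked for good compliance; the text simply gives no rule. Nor will follow-up data exist for all 376 per group, given the valid-day rule and the assumed 20% loss. That is why 300 is used above.

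**Conclusion.** The point holds as a conflict to be reconciled and an efficiency gain left unused. It is not an arithmetic error, since 47 and 59 are correct for what they size. It concerns a secondary outcome and leaves the MACE analysis untouched.

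If the 59 is applied literally, the interval for sedentary time is about 2.5 times as wide as with the full set, in a subset with no selection rule. If every participant with valid data is analysed, as Secondary outcomes implies, that loss disappears and only the wording needs correction.

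The second part applies either way: which visit is tested, and how T0 and the profile enter, should be stated. T0 activity recordings are needed to randomise anyone, so using them costs almost nothing.

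These sizes assume that the pilot SD applies to the trial population, that about 20% are lost at the visit analysed, and that rho is as shown. They describe raw sedentary minutes at one visit and only illustrate the gain for the log-ratio analysis.

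**What to change.** 1. Under Sample size, state that 59 per group is the minimum needed for the comparison of sedentary minutes, and that all randomised participants with valid ActivPAL data will be analysed. If a sub-sample really is intended, state a selection rule fixed before follow-up data are seen, and bring Secondary outcomes and Table 3 into line.
2. Under Statistical analysis, model the log-ratio coordinates at T1, T2 and T4 by arm and visit, adjusted for the T0 coordinates and the sedentary profile used for stratification. A multivariate mixed model does this. A MANCOVA at one named main visit is a simpler alternative that stays close to the present plan.
3. Name the main visit and the joint test of the arm effect, and report contrasts back-transformed to minutes per day.

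The cost is a few sentences and slightly more programming. No new data, visits or participants are needed.
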